The key aims of the groups are to encourage goal setting, self-monitoring and behavioural self-regulation, improve motivation and boost self-efficacy and social support. These are addressed directly by the Slimming World approach. Intervention staff will also be trained by the study team on the importance of encouraging and supporting women with respect to these aims. Women will be encouraged to weigh at least weekly and to monitor and, if necessary, alter their eating and physical activity behaviours in relation to their goals. The groups seek to enhance women’s motivation by providing positive feedback and by helping them set realistic goals, problem solve and manage lapses or setbacks appropriately. It is intended that the groups will improve women’s self-efficacy by providing them with useful information and by helping them develop the necessary skills for a healthy lifestyle, but also by helping them build on success and by giving them opportunities for observing similar others succeeding (modelling) as well as providing positive feedback on progress [72]. Social support will be provided by other women within the groups as the setting facilitates sharing experiences and information, giving feedback, empathy and encouragement as well as reinforcement of behaviours which may help increase motivation. It also provides opportunities for role modelling, improved self-efficacy, instrumental support (help), appraisal (e.g. affirmation) and peer pressure for healthy behaviours.

Regular attendance at the groups will be encouraged and participants will be contacted if they miss two or more consecutive intervention group sessions, to try to foster future attendance. Intervention group sessions will be held at a convenient time to enhance attendance, usually early evening.

The Intervention Midwives and Slimming World consultants will attend a one day training workshop delivered by the study team and will receive a study manual detailing all aspects of the intervention, in order to ensure consistency in the delivery of the intervention across all sites. In addition, intervention group sessions will be observed by study team members to examine intervention fidelity across sites.

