**Secondary outcomes**		
Antenatal and birth complications**	Routinely collected data held in patient records	Birth
Pregnancy weight gain	Calibrated adult scales	B, 36w
Waist circumference and waist-hip ratio	Measuring tape	12 m
Child weight centile (adjusted for birth weight and age)	Calibrated baby scales and measuring tape	Birth, 6p, 6 m, 12 m
Admission to neonatal unit	Patient records	Birth
General mental health	General Health Questionnaire (GHQ) 12 [82]	B, 36w, 6p, 6 m, 12 m
Breast feeding intentions	Study-developed questions	36w
Breast feeding behaviour and weaning	Study-developed questions	6p, 6 m, 12 m
Self-reported physical activity	7 Day Physical Activity Recall (7 Day PAR) [83-85]	B, 36w, 6p, 6 m, 12 m
Diet	Dietary Instrument for Nutrition Education (DINE) [86] (plus additional questions on fruit and vegetables, sugar, sweets)	B, 36w, 6p, 6 m, 12 m
Alcohol	Alcohol Use Disorders Identification Test-Consumption (AUDIT-C) [87]	B, 36w, 6p, 6 m, 12 m
Smoking	Study-developed questions	B, 36w, 6p, 6 m, 12 m
Costs	Participant resource use	B, 36w, 6p, 6 m, 12 m
Health related quality of life	EQ-5D (including visual analogue scale) [88]	B, 36w, 6p, 6 m, 12 m

*B = baseline; 36w = 36 weeks gestation; 6p = 6 weeks postpartum; 6 m = 6 months postpartum; 12 m =12 months postpartum.

**gestational diabetes; pre-eclampsia; thrombosis; proportion staying within IOM guidance on weight gain in pregnancy [20]; form of pain relief; birth delivery mode; gestation at delivery; induction of labour; shoulder dystocia, 3^rd^/4^th^ degree perineal tear; postpartum bleeding or thrombosis; Apgar scores.

**Table 2 T2:** Measurement of Mediators

**Mediators**	**Measure**	**When**
Social support	Social Support Exercise and Eating Habits Scales [89] (plus intervention specific social support questions)	B, 36w, 6 m, 12 m
Self-efficacy	Weight Efficacy Lifestyle Scale [90] and Multidimensional Self efficacy for Exercise Scale [91,92]	B, 36w, 6 m, 12 m
Self-regulation	Shortened Self-Regulation Questionnaire [93]	B, 36w, 6 m, 12 m
Motivation	Treatment Self-Regulation Questionnaire (for diet and physical activity) [94]	B, 36w, 6 m, 12 m

(B = baseline; 36w = 36 weeks gestation; 6 m = 6 months postpartum; 12 m =12 months postpartum).

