A key method for assessing these components is via the qualitative data collection i.e. qualitative interviews with participants and focus groups with the staff delivering the intervention. Semi-structured interviews will be completed with approximately 30 participants from the intervention group, purposively sampled across sites according to attendance levels at the intervention group sessions and whether they lost weight or not. The interviews will be carried out at the end of the intervention period (at approximately 6 months postpartum) and at the end of the study (at approximately 12 months postpartum). We will explore the participants’ views of the intervention, barriers and facilitators, the impact of life events on adherence to the intervention, importance of social support, strategies, coping mechanisms and responses to relapses. We will interview a small sample of participants who drop out of the intervention but who are willing to be interviewed, to establish their views of the intervention and reasons for discontinuing. We will also conduct brief interviews with a sample of around 15 women from the control group about taking part in the study and any lifestyle changes they made both during and after pregnancy. The interviews will continue until data saturation is reached.

Three intervention staff focus groups will be completed and will explore the intervention components, the delivery of the intervention, intervention fidelity, participant adherence to the intervention, the recruitment process, perceived challenges or barriers in implementing the intervention and potential improvements to the intervention or the training.

With regards to theory testing we developed a logic model (this is shown in Figure 1) to explain the processes by which the intervention brings about change and we plan to test the theory of our intervention via mediation analyses as well as through other aspects of the process evaluation including participant interviews. Potential mediators including self-regulation, intrinsic motivation, self-efficacy and social support will be assessed. The analyses will identify both the extent to which the intervention was successful at changing these mediators and the extent to which mediator change was associated with change in BMI. Potential moderators of intervention effect will be examined including demographics, ethnicity, parity, mental health (also an outcome), smoking status and weight loss history.

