### Analysis

#### Quantitative analysis

The main analysis will be by intention to treat and will compare the primary outcome of BMI at 12 months postpartum in the intervention and control groups. Multilevel modelling will be used to account for clustering within antenatal unit and individual effects. A two level linear regression model will include baseline BMI (measured at recruitment) as a covariate. Both levels will be considered ‘random effects’ i.e. patients and units are drawn randomly from a larger population of patients and units. Cluster level variables include those used to balance the randomisation: antenatal unit size; proportion of women with BMI +/=30, geographic location and ethnic mix.

For the BMI data, positively skew distributed form is anticipated and will be checked prior to analysis. Log transformation will be considered, not only to deal with the non-normality but to allow interpretation of differences between arms in percentage terms. To further aid clinical interpretation of the intervention effect, analysis of log transformed weight at 12 months postpartum will also be considered, with baseline log weight and log height as covariates. The results can then be expressed in terms of BMI or weight along with a 95% confidence interval. The intra-cluster correlation (ICC) for the primary outcome will be calculated and reported.

Intention to treat analysis will be used for all secondary outcomes. Analysis of secondary outcomes will also use multilevel modelling incorporating baseline scores as covariates where appropriate. Two level linear regression models will be used for outcomes such as pregnancy weight gain and waist-to hip ratio and validated questionnaire scores, while logistic models will be used for clinical event outcomes. 95% confidence intervals for the intervention effect will be calculated. The ICC for each secondary outcome will be calculated and reported.

The impact of individual demographic factors as well as theoretical mediators (self-efficacy, social support, intrinsic motivation and self-regulation) on the intervention effect using interaction terms included in the main analysis models will be examined. Individual demographic variables include age, ethnicity, smoking status, previous weight loss history, psychological wellbeing and social class. We also intend to carry out tests for mediator variables [97].

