As well as examining number of sessions attended, patterns of missed sessions and compliance with the intervention will also be explored. A complier average causal effect (CACE) analysis will be carried out for the primary outcome to assess the effect of the intervention in those who complied [97,98]. An investigation of required minimum dose of intervention will be carried out. A per- protocol analysis will include only those participants in each arm that received treatment as randomised excluding those in the control arm attending weight loss groups.

No formal subgroup analyses are planned. However, exploratory analyses of the impact of social class, parity, ethnicity (if numbers permit), smoking status and initial BMI on the effect of the intervention will be carried out. This will be achieved by fitting a subgroup by randomised group interaction term to the multilevel model.

If the proportion of missing primary data is substantial (more than 10%) a series of sensitivity analyses will be carried out to determine the likely effects of missing data [99-101]. The intention is to use multiple imputation to generate complete datasets for analysis. Imputation models will include those variables in the analytic model plus any additional variables associated with missingness and outcome. Self-reported weight (from the minimum dataset) and Slimming World session weight data may be used to replace missing weights where appropriate in secondary analyses. Further sensitivity analyses may be carried out to examine the effects of removing women who are known to be pregnant at the 12 month postpartum follow-up, as well as those who have recently given birth to a second baby. The assumptions of all models used for primary and secondary analysis will be checked.

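### The birth, antenatal and neonatal event models get no individual-level covariate; parity, planned only for interaction analyses, should be prespecified as one because women appear to consent after their unit is allocated

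*Protocol article*

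**What the plan says.** Under Quantitative analysis, the primary BMI model has a named individual-level covariate: "A two level linear regression model will include baseline BMI (measured at recruitment) as a covariate". The same paragraph lists the cluster-level variables used to balance randomisation: unit size, proportion of women with BMI of 30 or more, location and ethnic mix. For secondary outcomes the rule is: "Analysis of secondary outcomes will also use multilevel modelling incorporating baseline scores as covariates where appropriate". The section adds that "logistic models will be used for clinical event outcomes".

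Table 1 gives the source of antenatal and birth complications as "Routinely collected data held in patient records", with birth as the only time point. Its footnote includes "birth delivery mode; gestation at delivery; induction of labour; shoulder dystocia", among others. Neonatal unit admission is also taken from records at birth.

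Parity appears in two places. Process evaluation says: "Potential moderators of intervention effect will be examined including demographics, ethnicity, parity, mental health (also an outcome), smoking status and weight loss history". Later in Quantitative analysis the plan describes "exploratory analyses of the impact of social class, parity, ethnicity (if numbers permit), smoking status and initial BMI on the effect of the intervention", to be done with interaction terms. Parity is not among the Site randomisation balancing factors, and no model names it as a main-effect covariate.

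**The concern.** A rule built on baseline scores works for questionnaires and weight. It supplies nothing for an event that happens once. The article therefore leaves these event models without any individual-level covariate, while the primary model has one.

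This matters more here than in an individually randomised trial. Only units are randomised, and balancing is on unit-level factors. Three sections together imply that a woman decides whether to join once her unit's arm is fixed. Site randomisation says clinics learn their allocation after site recruitment. Participant recruitment places consent at a home visit arranged by the unit's research midwife. Study intervention lets women attend groups from the point of recruitment. Women in the two arms are then agreeing to different things: usual care with leaflets, or the same plus a weekly group of an hour and a half. If willingness to join depends on having children already, parity could differ systematically between arms.

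Fewer complications in pregnancy, at birth and postnatally is the second secondary aim. If event risk also depends on parity, an unadjusted comparison would mix that difference with the effect of the intervention.

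**Working it through.** **The plan's own figures.** The article's sample size is for BMI and reproduces. A two-sample t-test for an effect of 0.333 SD at 80% power and 5% significance needs 142.5, so 143 per group. Then 286 × 1.4 = 400.4, and 400 / 0.70 = 571, against the stated 570. No figure is given for birth or complication outcomes, so nothing stated is contradicted.

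**Inputs for the illustration**

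- From the documents: 570 women and 20 units, hence 285 women and 10 units per arm, 28.5 women per unit; ICC 0.02. The ICC is the one assumed for BMI and is borrowed here for binary events.
- Assumed, not in the documents: 40% nulliparous overall, no true intervention effect, a systematic imbalance of 15 points (47.5% v 32.5% nulliparous), and three pairs of event risks by parity group. Which group is given the higher risk only sets the sign.

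**Formulas**

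- Design effect = 1 + (28.5 − 1) × 0.02 = 1.55.
- Spurious risk difference = parity imbalance × risk difference between parity groups.
- SE of the risk difference = √(2 × p(1 − p) / 285 × 1.55), with p the mean event risk. This approximates the multilevel model.

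**Results for a 15-point imbalance**

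| Assumed risks by parity group | Mean risk | Spurious difference | SE | Difference / SE | False-positive rate |
|---|---|---|---|---|---|
| 15% v 10% | 12% | 0.15 × 5 = 0.75 points | 3.39 | 0.22 | 5.6% |
| 30% v 15% | 21% | 0.15 × 15 = 2.25 points | 4.25 | 0.53 | 8.3% |
| 40% v 10% | 22% | 0.15 × 30 = 4.5 points | 4.32 | 1.04 | 18.1% |

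A 5-point imbalance gives 0.25, 0.75 and 1.5 points. With 200 women per arm (design effect 1.38) the shifts are unchanged and the SEs are 3.82, 4.78 and 4.87.

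**Chance imbalance, for scale.** The SD of the arm difference in nulliparous share is √(2 × 0.4 × 0.6 / 285 × design effect): 4.1 points at ICC 0, 5.1 at ICC 0.02 and 6.3 at ICC 0.05. Over repeated randomisations this variation is part of the model's standard error. The false-positive rates in the table apply only to an imbalance that is systematic.

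**The case against.** The strongest reply is that covariates for each secondary model are ordinary analysis-plan content, that the rule's closing qualifier leaves room for judgement, and that an unseen plan may add parity. A reader might infer that the article rules out adjusting for parity. It does not. What remains is that the article does state a covariate rule, and that rule supplies none for this group of outcomes. The cluster-level variables would not cover parity even if carried over.

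A reader might also infer that first-time mothers will be over-represented in the intervention arm and that their higher risk will hide a benefit. The documents support neither step. They give no parity distribution and no event risks by parity. On session timing they say only: "Intervention group sessions will be held at a convenient time to enhance attendance, usually early evening". That consent follows allocation is itself read from three sections together, and that parity is recorded is inferred from its planned use.

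Nor can chance imbalance between 20 units be counted as bias. That part of the objection stands in full. So does the point on precision: in a logistic model, adjustment does not reduce the standard error of the log odds ratio, so no gain is claimed.

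There are safeguards. The midwife delivering the intervention does not decide whom to approach, screening forms record who declines and at what stage, and the process evaluation compares eligible with recruited women. These limit staff selection and may reveal differential enrolment. They do not prevent women's own selection or correct the estimate.

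Finally, age, smoking or initial BMI could be proposed on similar grounds. Parity is not the only defensible choice, but it is one the plan already intends to use, and the present rule reaches none of the others for these outcomes either.

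**Conclusion.** The point holds as a modest one. As worded, the covariate rule gives the once-only antenatal, birth and neonatal events no individual-level adjustment, and parity enters only through interactions. Recruitment that appears to follow allocation makes a systematic difference in parity possible; the documents do not show that one will occur or in which direction.

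Under the stated assumptions, a systematic 15-point imbalance moves the risk difference by 0.75 points when parity groups differ by 5 points in risk, and by 2.25 to 4.5 points when they differ by 15 to 30. That is from about a fifth of a standard error to about one. Smaller imbalances matter proportionately less.

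An unadjusted intention-to-treat comparison would be a legitimate analysis if selection does not differ by arm. Adjusting for parity would remove only the part of any selection that works through parity. The primary BMI analysis is not affected, and a reader should not extend the concern to it.

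**What to change.** In Quantitative analysis, after the sentence on secondary-outcome covariates, state that the multilevel logistic models for antenatal, birth and neonatal outcomes with enough events to support it will include parity (nulliparous v parous) as a fixed individual-level covariate. Report a standardised risk difference from that model, with the unadjusted estimate alongside. For very rare events report counts by arm without a model.

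The cost is a sentence or two of analysis wording. No new data should be needed, since the planned interaction analyses already require parity. The drawback is that the adjusted odds ratio is conditional on parity; the standardised risk difference deals with that. Naming the covariate in advance also avoids choosing it after any imbalance has been seen, which matters where the article itself expects that blinding outcome collectors will be difficult.

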With regard to pregnant obese or overweight women, a recent large randomised controlled trial (RCT) found no impact of a lifestyle intervention on gestational weight gain (GWG) or on the proportion of women whose weight gain was below or within IOM guidance [32]. The intervention did not reduce the risk of large for gestational age infants nor did it improve maternal outcomes. However, the intervention was associated with a reduction in the risk of birth weight above 4000 g. A recent high quality meta-analysis of RCTs of interventions of diet and physical activity, alone or in combination, which included studies where women were obese, overweight and normal weight, found an overall 1.42 kg difference between intervention and control participants in GWG (in favour of the intervention group) [33]. For diet alone the difference was 3.84 kg. For interventions targeting obese or overweight women only the reduction in GWG was 2.1 kg. This review also found that reductions in pregnancy weight gain were not associated with an increased rate of small for gestational age babies. Interventions were associated with a lower risk of pre-eclampsia and shoulder dystocia and there was a trend towards a reduction in gestational diabetes, gestational hypertension and pre-term birth. However, the quality of the evidence was low for clinical outcomes as there was evidence of significant heterogeneity in the effect size, study level biases including issues with randomisation, incomplete outcome data, blinding, as well as risk of publication bias [33]. Other systematic reviews and meta-analyses have also found lower GWG from diet and physical activity interventions, but included studies often had methodological limitations including high loss to follow-up, small sample sizes and problems with blinding [34-38]. A Cochrane review of interventions to prevent excessive weight gain during pregnancy concluded that due to small effect sizes and methodological limitations of studies no intervention could be recommended for limiting excessive GWG [39].

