### Participant recruitment

570 pregnant women with a Body Mass Index (BMI) of +/=30 aged 18 years or older and between 12 and 20 weeks gestation will be recruited. Potentially eligible participants will be approached at their earliest antenatal appointment by NHS midwives or researchers, who will provide an information sheet and briefly describe the study. The decision to approach women will not be made by the midwife delivering the intervention. If women are eligible and interested in participating, they will be contacted by the research midwife (local Principal Investigator (PI)) to discuss the study in greater detail and arrange a baseline home visit where informed consent and baseline measures will be taken.

The approaching midwife/researcher will provide the women with a comprehensive information sheet prior to the baseline visit and adequate time will be given for them to read the material and to ask any questions they have about the study. Women will be reminded that they retain the right to withdraw consent for participation in any aspect of the trial at any time without their routinely available NHS care being affected. Midwives/researchers will be trained in Good Clinical Practice and all study procedures. The participant’s GP, named midwife and obstetrician, if applicable, will be informed that she is taking part in the study.

A screening form will be completed to record the number of women approached about the study, eligibility, and at what stage women declined to take part in the study (e.g. when first approached or at the consent stage).

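### Pregnancy weight gain and the 5% weight-loss proportion start from a weight taken anywhere between 12 and 20 weeks, and the stated adjustments do not allow for gestation at that visit

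*Protocol article*

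**What the plan says.** Under Participant recruitment, women "aged 18 years or older and between 12 and 20 weeks gestation will be recruited". After the first approach the research midwife is to "arrange a baseline home visit where informed consent and baseline measures will be taken"; no gestational week is set for that visit. The first approach is to be at the earliest antenatal appointment.

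Table 1 gives the measurement points of the weight-gain outcome: "Pregnancy weight gain Calibrated adult scales B, 36w". The Quantitative analysis section also plans, for each arm, the proportion who lost 5% of their weight, comparing weight at 6 months postpartum with baseline.

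For secondary outcomes that section describes multilevel models "incorporating baseline scores as covariates where appropriate. Two level linear regression models will be used for outcomes such as pregnancy weight gain". The primary model for BMI at 12 months postpartum has baseline BMI, measured at recruitment, as a covariate. The section also names the four cluster-level variables used to balance the randomisation. Gestation at baseline is not named as a covariate, as a balancing factor (Site randomisation) or as an exploratory factor.

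Clinics are told their allocation after site recruitment. The article does not say that women are recruited before then.

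**The concern.** An outcome that carries one name covers different lengths of pregnancy in different women. A woman weighed first at 20 weeks has already put on weight that counts as gain for a woman weighed first at 12 weeks. For the 5% outcome the later start is a heavier start, so the threshold is easier to reach.

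Within an arm this is noise. Between arms it becomes a shift in the treatment contrast if mean gestation at the baseline visit differs. Only 20 units are randomised, timing may vary from unit to unit, and units know their arm while they recruit. Lower weight gain in pregnancy is the first secondary aim listed, so the contrast matters.

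**Working it through.** **From the article:** recruitment at 12 to 20 weeks; gain measured from baseline to 36 weeks; 10 units per arm with an average of 20 women each in the sample-size section; a primary difference of 1.5 kg/m² (SD 4.5). The benchmark for weight gain is in Obesity interventions: "For interventions targeting obese or overweight women only the reduction in GWG was 2.1 kg".

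**Assumed, not in the article:** weekly gain 0.2 to 0.5 kg; height 1.65 m; slope of the later weight or BMI on baseline 0.8 to 1.0; recruitment spread evenly over the window; SD between units in mean gestation at baseline 0.5 to 2 weeks.

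1. *The article's own figures.* The effect size is 1.5/4.5 = 0.333, which needs 142 to 143 women per group. Then 286 × 1.4 = 400, and 400/0.7 = 571 against the stated 570. These reproduce and are not in dispute; 1.5 kg/m² serves below only as a yardstick.
2. *Length of the gain interval.* 36 − 12 = 24 weeks and 36 − 20 = 16 weeks, a ratio of 1.5.
3. *Spread from timing alone.* The same weight trajectory is recorded 8 × 0.2 = 1.6 kg to 8 × 0.5 = 4.0 kg differently across the window. With even recruitment the SD of gestation is 8/√12 = 2.31 weeks, which corresponds to an SD of 0.46 to 1.15 kg in measured gain.
4. *Shift from an arm gap.* Shift = gap in mean gestation × weekly gain. For one week this is 0.2 to 0.5 kg, and 0.2/2.1 to 0.5/2.1 = 10 to 24% of the benchmark. Baseline weight as a covariate does not repair it: the shift is only multiplied by the baseline slope. At 0.8 it is 0.16 to 0.40 kg; at 1.0 it is unchanged.
5. *Size of a chance gap.* With between-unit SD s and within-unit variance w² = 64/12 − s², SE = √[2(s²/10 + w²/200)]. For s = 1, w² = 4.33 and SE = 0.49, so the 95% range is ±0.97 week. That is 0.19 to 0.48 kg, or 9 to 23% of 2.1 kg. For s = 0.5 the range is ±0.62 week (0.12 to 0.31 kg); for s = 2 it is ±1.77 weeks (0.35 to 0.88 kg).
6. *The 5% outcome.* For illustration, a BMI of 35 at 1.65 m is 35 × 2.7225 = 95.3 kg, and 5% of that is 4.8 kg. A baseline at 20 rather than 12 weeks adds 1.6 to 4.0 kg to the recorded loss, 34 to 84% of the threshold. The threshold itself rises by only 0.08 to 0.20 kg.
7. *Primary BMI.* One week of arm gap shifts baseline BMI by 0.2/2.7225 = 0.07 to 0.5/2.7225 = 0.18 kg/m². Times the slope, the adjusted contrast moves by 0.06 to 0.18 kg/m², or 4 to 12% of 1.5.

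**The case against.** The article condenses the plan. It gives no closed covariate list for weight gain, and a statistical analysis plan that is not shown may include gestation. This lowers the certainty but does not remove the point: the floating start is fixed here by the recruitment window, Table 1 and the definition of 5% loss, and none of the adjustments that are named corrects for it.

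Units are randomised, so timing is balanced in expectation. A chance gap adds between-unit variation, which the two-level model carries into the confidence interval. That stands. Chance imbalance mainly costs precision, and systematic bias needs timing to respond to allocation.

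Nothing in the article shows such a response. Both arms approach women at the earliest appointment, and the intervention midwife does not decide whom to approach. This narrows the window in practice but does not fix the week of the baseline visit.

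A reader might infer that intervention units, whose groups start at recruitment, would enrol early and so produce a false benefit. The direction is the reverse. Earlier enrolment lengthens their interval to 36 weeks and raises their measured gain. It also lowers their starting weight, which makes 5% loss harder to reach. It would hide a benefit, not create one.

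**Conclusion.** The point holds for pregnancy weight gain and for the 5% weight-loss proportion. The 16- to 24-week interval follows from the article alone. The 0.2 to 0.5 kg shift per week of arm gap rests on the assumed weekly gain, and whether a gap will arise is unknown. Without a gap, what remains is a loss of precision.

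Three stronger readings are not supported:

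- **A two-week gap.** This would give 0.4 to 1.0 kg, 19 to 48% of 2.1 kg, but it is a quarter of the whole window and has no source in the article. A chance gap near one week is already at the 95% limit when the between-unit SD is 1 week.
- **The primary result depends on when units recruit.** The primary outcome is BMI at 12 months postpartum, not a change from baseline. Varying gestation within arms mainly adds noise to a covariate. Only an arm gap shifts the contrast, and modestly.
- **Guideline adherence is judged on the truncated gain.** The "proportion staying within IOM guidance on weight gain in pregnancy" stands in the footnote to the complications row of Table 1, whose source is "Routinely collected data held in patient records" and whose time point is birth. The article gives no start weight for it and does not say that the baseline visit is used.

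**What to change.** - Add gestational age at the baseline visit, or weeks between the two weighings, as a covariate in the pregnancy-weight-gain model, and gestational age at baseline in the analysis of 5% loss.
- Report gestation at the baseline visit by arm.
- Add gestation at baseline to the primary BMI model as a sensitivity analysis.
- State the start weight for adherence to the weight-gain guidance. Use gain per week over the observed interval only if that start is the baseline visit.

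Gestation must be known to confirm eligibility, so this needs no new visit and no change in sample size. The cost is a few lines of wording.
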